##### Intensified social counseling

Additional social counseling is carried out by a social worker in group and in individual sessions. It is aimed at the clarification of the problematic work-related situations and perspectives of WMR patients by providing them with extra information and advice on social law and services. The social worker develops the RTW framework jointly with the patient and identifies which additional measures and benefits are needed and available to achieve RTW in each specific case. Such measures and benefits cover a broad scale of possible instruments and range from modifications of the work environment (e.g. height-adjustable desks) through vocational retraining (e.g. achieving a new professional title), to wage substitutes. The social worker requests the individually indicated measures and benefits from the social or health services agencies (e.g. GPI, health insurance, integration office). If needed and wanted by the patients, the social worker also establishes contact with the employer to facilitate the transition from the rehabilitation center back to the workplace (e.g. by initiating graded RTW or modifications of the work environment). The group sessions take at least 60 min. The personal counseling takes at least 30 min.

### Participants

Cancer patients (ICD-10: C00-D48) aged 18 to 60 years are included in the study if they have a score of ≥70 % on the Karnofsky Performance Status Scale [50, 51] and a preliminary positive social-medical prognosis of employability for at least 3 h/day within the next 6 months as assessed by the rehabilitation physician in the initial examination after starting the rehabilitation program. Moreover, patients are only eligible to participate if they have an elevated risk of not returning to work. This risk is assessed by the Screening Instrument Work and Occupation (German: Screening-Instrument Beruf und Arbeit in der Rehabilitation, SIBAR) [52–54]. This screening consists of three subscales. The first subscale is a 9-item scale and assesses the risk of health-related early retirement on the basis of a weighted sum score of several risk indicators (e.g. sick leave duration and the patients’ belief of time to return to work). A score of more than 7 out of 19 possible points indicates an elevated risk of early retirement and thus a need for a WMR program. The second subscale is a 1-item score and assesses the amount of perceived job strain. The third scale is also a 1-item score and assesses the subjective need for work-related therapies during the rehabilitation program. If patients indicate a very stressful job situation or assume that work-related therapies will be very helpful, this is also taken as a marker of the need for a WMR program. In brief, patients are included if one of the three scales indicates a need for a WMR program. Previous studies estimated that this is the case for about half of the patients. Moreover, about a quarter of the patients has an elevated risk of early retirement based on the first scale of the SIBAR [52–54]. No exclusion criteria were defined.

### Randomization

The study is designed as a cluster-randomized multicenter trial. Patients are recruited from four inpatient rehabilitation centers. Patients of a rehabilitation center who start their rehabilitation in the same week represent a cluster. These patients jointly receive either the intervention or the control treatment. Cluster-randomization was chosen to avoid spillover effects between therapy groups. Each of the four rehabilitation centers receives its own randomization schedule. The randomization lists are created by the last author using computer-generated random numbers and blocks of 4. The administrative employees who assign the patients to their date of rehabilitation are blinded to the randomization schedule.

### Sample size calculation

Sample size calculation was done to detect a standardized mean difference (SMD) of SMD = 0.3 in the primary outcome with 80 % power and a two-sided alpha error of 5 %. Using a t-test, a sample size of 352 participants would be needed. The planned regression modeling of treatment effects, which includes the baseline measurement of the primary outcome as a covariate, needs a sample size that is reduced by the factor 1 - r^2^ [55]. The correlation r represents the correlation between baseline and follow-up measurement. The approximation of the sample size based on a t-test represents a conservative proxy, even when considering the design effects induced by the cluster-randomization or missing values. Based on expected sample attrition due to nonresponse to the 1-year follow-up questionnaire of 30 %, we aim to recruit at least 504 patients.

### Outcome measures

Primary and secondary outcomes are assessed by questionnaires at the beginning of the inpatient rehabilitation program, at discharge from the rehabilitation program, and 3 and 12 months after discharge. Questionnaires at the beginning and discharge of the program are delivered and collected by study nurses in the rehabilitation centers. These nurses are not blinded to the treatment allocation. Questionnaires at 3- and 12-month follow-up are sent by mail to the first author who is also not blinded to the treatment allocation. Table 3 shows all variables and their corresponding measurement point.

**Table 3 Tab3:** Time schedule of assessments and instruments

	Admission	Discharge	3-month follow-up	12-month follow-up
Role functioning (EORTC QLQ-C30) [56]	X		X	X
Physical functioning (EORTC QLQ-C30) [56]	X	X	X	X
Emotional functioning (EORTC QLQ-C30) [56]	X	X	X	X
Social functioning (EORTC QLQ-C30) [56]	X		X	X
Pain (EORTC QLQ-C30) [56]	X	X	X	X
Global health (EORTC QLQ-C30) [56]	X	X	X	X
Fatigue (EORTC QLQ-FA13)	X	X	X	X
Coping with illness (FCQI) [60]	X	X	X	X
Implementation of work-related therapies [63]		X		
Consistency of work-related rehabilitation strategy [63]		X		
Benefit from work-related therapies [63]		X		
Work Ability Score [59]	X	X	X	X
Employment status	X		X	X
Time of return to work			X	X
Sick leave duration	X		X	X
Disability days during the last 3 months [61]	X		X	X
Patient satisfaction [64]		X		
Sociodemographic data	X			
Discrete choice experiment	X			
Screening Instrument Work and Occupation [67]	X			

*EORTC QLQ-30* 30-item quality-of-life questionnaire of the European Organization for Research and Treatment of Cancer; *EORTC QLQ-FA13* 13-item fatigue questionnaire of the European Organization for Research and Treatment of Cancer; *FCQI* Freiburg Questionnaire of Coping with Illness

In the case of nonresponse to the follow-up questionnaires at 3 and 12 months after discharge, participants receive three additional reminders. The first reminder consists of a letter and is sent one week after the initial follow-up questionnaire; the second reminder includes the questionnaire again and is sent three weeks after the initial follow-up questionnaire; the third reminder also includes the questionnaire again and is sent six weeks after the initial follow-up questionnaire.

### Main study outcome

The primary outcome of the study is the role functioning scale of the 30-item quality-of-life questionnaire of the European Organization for Research and Treatment of Cancer (EORTC QLQ-30). The role functioning scale comprises two items that relate to a) work and other daily activities and b) hobbies and leisure time activities. Response categories are “not at all,” “a little,” “quite a bit,” and “very much.” Single-item scores will be averaged and transformed to a score from 0 to 100 points. Higher scores represent better functioning [56].

### Secondary study outcome

Secondary outcome measures are additional scales of the EORTC QLQ-30. These scales measure physical functioning, emotional functioning, social functioning, pain, and global health [56, 57]. Additionally, we use the 13-item fatigue module (EORTC QLQ-FA13) [58]. All scales range from 0 to 100 points. Higher scores indicate a better health-related quality of life.

Self-rated work ability is measured with the Work Ability Score. Ten points represent the best work ability ever achieved; 0 points indicate total work disability [59].

Disease coping is measured with three scales of the Freiburg Questionnaire of Coping with Illness (FCQI; depressive coping, active coping, distraction, and self-encouragement) with 5-point scaled items [60]. Raw item scores will be added up to a sum score for each scale. These will be used to calculate a mean scale score, resulting in values ranging from 1 to 5 points [60].

Participation in working life is measured with an assessment of the current employment status, current sick leave status, and disability days during the last 3 months [61, 62]. The assessment after 12 months also includes a question regarding the date of initial return to work.

The realization of work-related goals and therapies during rehabilitation is assessed with a slightly modified version of a previously used set of items from a study that investigated the implementation of the WMR guidelines [63]. Participants report on 12 dichotomized items whether they received WMR contents throughout their rehabilitation program. Scores are aggregated to a total score ranging from 0 to 12 points. This score reflects the implementation of the work-related therapies. Additionally, 6 items assess the perceived diagnostic and therapeutic focus on issues of return to work and work ability, e.g. the experience of a consistent RTW strategy. These items are 5-point scaled. Scores will be summed to a total score ranging from 0 to 24 points. Finally, the subjective work-related benefit from participating in the rehabilitation program is assessed with 8 items using 5-point scales. Scores are aggregated to a total score ranging from 0 to 32 points.

Treatment satisfaction is assessed using the German version of the Client Satisfaction Questionnaire (CSQ-8) [64]. This questionnaire uses 8 items to assess various aspects of the patient’s satisfaction with the treatment. Items are 4-point scaled. The sum score ranges from 8 to 32 points.

### Supplemental data

The sociodemographic data that are assessed include age, sex, employment status, native language, partnership, number of children, educational level, and job qualification. Additionally, a discrete choice experiment is attached to the baseline questionnaire to assess patients’ treatment preferences [65].

### Data management

Questionnaires will be scanned and verified by an electronic data capture system and exported to statistical software packages for further analysis. Scanning and verifying is done by trained research assistants. Research assistants check electronically processed data item by item and compare imported data with the original questionnaire data.

If available, standard syntaxes are used to calculate scales (e.g. symptom scales of the EORTC QLQ-30) for further analyses. Each data set is checked for errors or inconsistencies before merging them with data from the other data sources or time points via the assigned study number to create a comprehensive data set. Data access is limited to the authors and the research assistants of the research team at the University of Lübeck.

### Statistical analysis

Treatment effects are tested using regression analyses. In the case of binary study outcomes, logistic regression will be used (e.g. effects on employment status or sick leave at follow-up). For analysis of time to return to work, we will use proportional hazard models. Baseline parameters will be considered as covariates [66]. Due to the cluster-randomization, the induced correlation of error terms for patients with the same arrival week will be taken into account by a random effect [67–69]. Rehabilitation centers will be considered using a fixed effect.

To calculate a SMD of the between-group difference, the unstandardized regression coefficient estimate of the treatment effect will be used [70]. This estimate will be standardized using the pooled standard deviation of the observed follow-up scores [71]. In the case of binary study outcomes, estimated odds ratios will be transformed into SMDs using a logit-transformation [71, 72]. SMDs will be interpreted as suggested by Cohen [73]: small effect: SMD ≥0.2, medium effect: SMD ≥0.5, large effect: SMD ≥0.8.

Furthermore, to test whether the treatment effect on the primary outcome is moderated by other variables we will include two-way interaction terms in the regression model. Potential moderators that will be tested are the remaining EORTC QLQ-30 scales, fatigue, the Work Ability Score, disease coping, and the type of rehabilitation (rehabilitation following primary cancer treatment vs. follow-up rehabilitation) as well as sociodemographic variables. Continuous moderators will be standardized using a z-transformation. The parameter estimate of the interaction between the z-standardized continuous score and the treatment indicator then represents the additional treatment effects when increasing the potential moderator by about one standard deviation [74–76]. Patients will be included in our analyses if they have completed the corresponding follow-up questionnaire and will be analyzed as randomized, i.e. as intended to treat [77]. Differences will be regarded as significant if the two-sided p-value of a test is less than 0.05.

Missing observations are excluded from the primary analysis. Supplementary analyses will impute missing observation by using the last observation carried forward method, in which the last observed value is used in place of the missing endpoint. No stopping guidelines are applied and no adverse health events are expected.

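### The primary analysis keeps only questionnaire completers under an intention-to-treat label; if non-response differs between arms, the 12-month effect can shift, and the 3-month scores that could limit this are not used in it.

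*Protocol article*

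**What the plan says.** The Statistical analysis section defines who is analysed: patients are "included in our analyses if they have completed the corresponding follow-up questionnaire and will be analyzed as randomized, i.e. as intended to treat". Shortly afterwards it adds: "Missing observations are excluded from the primary analysis". The model has baseline covariates, a random effect for arrival week and a fixed effect for centre. It names no post-baseline measurement. The one planned analysis of missing data is supplementary and uses LOCF.

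The Sample size calculation section builds in 30 % "expected sample attrition due to nonresponse to the 1-year follow-up questionnaire". Table 3 (Outcome measures) lists role functioning, the primary outcome, at admission, 3 months and 12 months, but not at discharge. The 3-month score is therefore the only intermediate measurement of the primary outcome.

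No primary time point is named. Because the sample size is tied to the 1-year questionnaire, 12 months is the reasonable reading, and it is assumed here.

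**The concern.** Two things are run together in the quoted sentence. Analysing patients in the arm to which they were randomised is one part of intention-to-treat; keeping all randomised patients in the comparison is the other. The plan does the first and not the second, so the label claims more than the analysis delivers.

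A patient who answers at 3 months but not at 12 has a known value of the primary outcome, and the primary 12-month analysis discards it. Follow-up is postal self-report, the two programmes differ in content, and those who collect the questionnaires are not blinded. It is plausible, though not shown, that response depends on how patients are doing and does so differently in the two arms. The completer contrast would then misstate the effect in all randomised patients. Recruiting extra patients to allow for non-response restores power but does nothing about such bias.

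**Working it through.** **1. The plan's own figures.** The inputs are the stated aim to "detect a standardized mean difference (SMD) of SMD = 0.3 in the primary outcome" "with 80 % power and a two-sided alpha error of 5" %. The normal approximation gives 175 per arm (350). The t-test gives 175.4, so 176 per arm, in agreement with "Using a t-test, a sample size of 352 participants would be needed". Equal allocation is assumed, as no ratio is stated. Allowing for 30 % loss, 352 / 0.70 = 502.9; by arm, 176 / 0.70 = 251.4, so 252 per arm and 504 in all, as in "we aim to recruit at least 504 patients". These figures reproduce.

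**2. Patients left out.** 0.30 × 504 = 151.2, so about 151.

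**3. Shift by formula.** Let d be the non-response share and D the mean of non-responders minus that of responders, in SD units given the covariates (1 = intervention, 0 = control). Then

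completer effect − effect in all randomised = −(d1·D1 − d0·D0).

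| d1, d0 | D1, D0 | Shift (SD) | Share of 0.30 |
|---|---|---|---|
| 0.30, 0.30 | −0.5, −0.5 | 0 | 0 % |
| 0.30, 0.30 | −0.2, 0 | 0.06 | 20 % |
| 0.30, 0.30 | −0.3, 0 | 0.09 | 30 % |
| 0.30, 0.30 | −0.5, −0.25 | 0.075 | 25 % |
| 0.25, 0.35 | −0.5, −0.5 | −0.05 | 17 % |

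For the last row: −(0.25 × −0.5 − 0.35 × −0.5) = −(−0.125 + 0.175) = −0.05. The shift comes from a difference between arms in rate or in deficit. Non-response that is merely related to outcome, equally in both arms, gives none.

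**4. Simulation, non-response depending on the 3-month score.** Assumptions: true SMD 0.30 at both follow-ups; 30 % missing at 12 months in each arm; correlation 0.4 between baseline and each follow-up, 0.6 between 3 and 12 months. The slope is the log-odds of non-response per SD of poorer 3-month score.

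| Slope, control | Slope, intervention | Completer estimate |
|---|---|---|
| 0.8 | 0.8 | 0.30 |
| 0.4 | 0.4 | 0.30 |
| 0.8 | 0.6 | 0.28 |
| 0.4 | 0.2 | about 0.275 |
| 0.8 | 0.4 | 0.26 |
| 0.8 | 0 to 0.2 | about 0.21–0.23 |
| 0 to 0.2 | 0.8 | about 0.36–0.40 |

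A model that uses the 3-month score returns 0.30 in every row.

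Under the strong pattern against controls, with 252 per arm, 15 % already missing at 3 months and 31–34 % at 12 months, the completer estimate was 0.23–0.25. Power fell from about 0.85 to 0.63–0.69, and type I error under the null was 8–11 %. These power and error figures belong to the strong pattern only.

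**5. What LOCF does.** Correlations here are 0.5 (baseline to each follow-up) and 0.7 (3 to 12 months), with all 3-month scores present.

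| Slope, control | Slope, intervention | Completers | Model with 3-month score | LOCF |
|---|---|---|---|---|
| 0.7 | 0.7 | 0.30 | 0.30 | 0.30 |
| 0 | 0.7 | 0.39 | 0.30 | 0.26 |
| 0.7 | 0 | 0.21 | 0.30 | 0.34 |

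Where the arms differ, LOCF misses on the opposite side from the completer analysis.

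**6. Limit of the remedy.** Let non-response depend instead on the unseen 12-month value, with slope 0.8 in controls and 0 in the intervention arm. With the correlations of step 4, completers give 0.12 and the model using the 3-month score about 0.17, against a true 0.30. The model helps but remains biased.

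**The case against.** The strongest case against is that the harm is conditional and the protocol does not establish the condition. A reader might infer that the completer analysis is valid only if 12-month non-response depends on nothing beyond baseline and arm. For the treatment contrast that is false: equal rates and equal slopes give 0.30, even when the slopes are steep. Both arms receive a full inpatient programme and the same three reminders, and nothing in the protocol predicts different non-response. It gives no arm-specific non-response, SD or correlation. This objection stands, and it limits the claim to what can happen.

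A reader might also infer that the plan ignores the 3-month data altogether or has no missing-data analysis. It has one: LOCF would carry the 3-month score forward, or the baseline score if 3 months is also missing. But it is only supplementary, and step 5 shows that it does not settle the matter.

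Nor is the exclusion concealed. The sentence that uses the label also states the restriction, and arm assignment is preserved. The fault is an imprecise label.

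Finally, it is tempting to call the 3-month score the best predictor of 12-month non-response. The protocol says nothing on that. The case for using the score is simply that it is an observed earlier value of the same outcome.

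**Conclusion.** The point holds as a should-fix. The primary analysis is a completer analysis that preserves allocation, not an analysis of all randomised patients, and at the planned non-response it omits about 151 of 504 from the 12-month comparison. The bias is zero when non-response behaves alike in both arms. Under the assumed patterns the estimate moves by 0.02–0.04 SD for mild between-arm differences (0.30 − 0.28 to 0.30 − 0.26) and by 0.06–0.10 SD for strong ones, that is, 7–13 % and 20–33 % of the 0.30 target, in either direction.

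These sizes rest wholly on assumed slopes and correlations and on reading 12 months as the primary time point. They do not show that the trial's result will be biased. They show that the plan relies on an unexamined symmetry between arms when data that would relax that reliance are already being collected.

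**What to change.** - Make the primary analysis a linear mixed model of role functioning at 3 and 12 months on all randomised patients. Terms: baseline role functioning, centre (fixed), time, treatment × time, a random effect for arrival week, and within-patient correlation. State that the 12-month contrast is the primary estimate, if that is what is intended.
- Multiple imputation by arm from baseline and 3-month data is an acceptable alternative. A patient with neither follow-up score adds no outcome information to the mixed model, so report how many there are in each arm.
- Keep the completer regression as a sensitivity analysis under that name, and reserve the intention-to-treat wording for the analysis of all randomised patients.
- Replace LOCF with a delta-adjusted analysis that shifts the values assumed for non-responders, separately by arm. This is needed because the mixed model and the imputation remove bias only when missingness depends on observed data.

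The cost is a change of wording and somewhat more analysis work, with no new patients, visits or questionnaires. The precision gain is small: about 4–7 % lower variance with correlations of 0.4 and 0.6 and 15 % missing at 3 months. The reason for the change is protection against bias, not power.

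### The only stated check on missing data, last observation carried forward, would use the pre-treatment admission score for anyone who misses both mailed follow-ups (0 to 151 of 504 patients)

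*Protocol article*

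**What the plan says.** Under Statistical analysis, the protocol article drops missing observations from the primary analysis and then adds: "Supplementary analyses will impute missing observation by using the last observation carried forward method". No other missing-data analysis is stated.

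Under Sample size calculation, the size of the problem is fixed in advance: "Based on expected sample attrition due to nonresponse to the 1-year follow-up questionnaire of 30" %, hence "we aim to recruit at least 504 patients".

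Under Outcome measures, prose and table disagree about the primary outcome. The section opens: "Primary and secondary outcomes are assessed by questionnaires at the beginning of the inpatient rehabilitation program, at discharge from the rehabilitation program", followed by the 3- and 12-month follow-ups. Table 3, which is presented as the full schedule, marks the row "Role functioning (EORTC QLQ-C30) [56]" at admission, 3 months and 12 months and leaves the discharge cell blank. Physical functioning, emotional functioning, pain, global health and fatigue are all marked at discharge. Both later follow-ups are by mail, with three reminders each.

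**The concern.** LOCF can carry forward only what was measured. If Table 3 is right, no role functioning score exists between admission and 3 months. A patient who returns the 3-month but not the 12-month questionnaire has the 3-month score held constant for nine months. A patient who returns neither has the admission score, taken before any treatment, entered as the 12-month result. For that patient the analysis asserts no change and no treatment effect. The admission score is also the planned baseline covariate, so outcome and covariate become the same number.

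This can do harm in three ways. A true effect is diluted. If nonresponse differs between arms and patients improve after admission, the arm with more nonresponse looks worse even when the programs are equally effective. And the filled values enter the model as if observed, so the standard error takes no account of the imputation. With 30% of 12-month scores expected to be missing, readers will look to this supplementary analysis for reassurance.

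**Working it through.** **The plan's own figures.** The stated target: "Sample size calculation was done to detect a standardized mean difference (SMD) of SMD = 0.3 in the primary outcome". Power is set at 80% and the two-sided significance level at 0.05. A two-sample t-test with 1:1 allocation (assumed; the ratio is not stated) needs 175.4, so 176 per arm and 352 in total, as the plan says. Inflating for 30% loss: 176 / 0.70 = 251.4, so 252 per arm and 504 in total. Both figures reproduce.

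**How many admission scores would be carried forward.** Expected without a 12-month score: 504 × 0.30 = 151. Let f be the share of these who also missed the 3-month questionnaire. The documents do not give f, so it is varied over its whole range. Number filled with the admission score = 504 × 0.30 × f.

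**Dilution.** Assume equal nonresponse by arm, no baseline difference, the full effect already present at 3 months, and SD 1. Then

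LOCF SMD = 0.70 × 0.30 + 0.30 × (1 − f) × 0.30 + 0.30 × f × 0 = 0.30 × (1 − 0.30 f).

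| f | Admission-score fills | SMD seen | Nominal power, 252 per arm |
|---|---|---|---|
| 0 | 0 | 0.30 | 92% |
| 25% | 38 | 0.278 | 88% |
| 50% | 76 | 0.255 | 82% |
| 75% | 113 | 0.2325 | 74% |
| 90% | 136 | 0.219 | 69% |
| 100% | 151 | 0.21 | 65% |

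The power column is a normal approximation without covariate adjustment or clustering. It counts every filled value as a real observation. For comparison, 176 observed patients per arm and an SMD of 0.30 give 80%. At half overlap LOCF therefore shows a smaller effect, yet slightly higher nominal power (82%), because imputed values are treated as data.

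**Unequal nonresponse, no true effect.** Assume 35% against 25% nonresponse and an improvement of 0.5 SD in both arms, complete by 3 months. Neither figure is in the documents.

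- Spurious difference = (0.35 − 0.25) × f × 0.5 SD: 0.05 SD at f = 100%, 0.025 SD at f = 50%.
- Simulated rejection rate (252 per arm, baseline-adjusted, no clustering, assumed correlations, 4,000 runs): about 10% at f = 100% and about 6% at f = 50%.
- With 0.8 SD improvement: 17–19% at f = 100%, about 8% at f = 50%. With 0.3 SD improvement: 6.9% at f = 100%.
- With equal nonresponse: near 5% even at f = 100%.

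**Unequal nonresponse, true SMD 0.30, f = 100%, control gain 0.3 SD (assumed).** With 35% missing in the intervention arm and 25% in control: 0.6 × 0.65 − 0.3 × 0.75 = 0.165. Reversed: 0.6 × 0.75 − 0.3 × 0.65 = 0.255.

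**The case against.** The strongest reply is about size. LOCF takes the 3-month score first, and Table 3 does schedule one. A reader might infer from the blank discharge cell that many 12-month values would be admission scores. The documents do not support that: they give no 3-month nonresponse rate and no overlap, and each mailing has three reminders. The supportable statement is 0 to 151. It is plausible that the same patients fail to answer both mailings, but that is an assumption.

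A reader might also infer that LOCF puts the false-positive rate at 10% or more. That needs full overlap, a 10-point difference in nonresponse and a sizeable improvement in both arms, all at once. The documents state none of these, and on improvement the Background is mixed: uncontrolled studies report gains in quality of life, while one controlled study found no lasting effect. At half overlap the inflation is small, and with equal nonresponse there is none.

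The complete-case analysis should not be read as vindicated. In these simulations missingness depends on arm only, so complete cases are unbiased by construction.

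It can further be said that LOCF is only supplementary, that a positive result surviving a diluting analysis still carries some information, and that imputation detail belongs in an analysis plan that is not shown. The first two points stand, so it would go too far to call the LOCF result worthless. The third does not remove the point, because the article itself names LOCF as the method.

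Finally, the opening prose of Outcome measures could be right and Table 3 wrong. The table looks deliberate, since social functioning is also blank at discharge, but the documents do not settle it. If a discharge score does exist, LOCF would seldom reach back to admission.

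**Conclusion.** The concern holds in a limited form. Under Table 3, the single stated supplementary analysis gives a pre-treatment score to every patient who misses both mailed follow-ups, freezes the 3-month score for the other 12-month non-responders, and treats all of these values as observed. That is a weak check on 30% missing primary data.

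Its size depends on an overlap that the documents do not give. A true SMD of 0.30 would appear as anything from 0.30 down to 0.21, with equal nonresponse by arm and the full effect present at 3 months. A spurious effect needs unequal nonresponse together with improvement after admission; under the assumptions shown it reaches at most 0.05 SD, with type I error about 10% at full overlap and about 6% at half.

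The primary complete-case analysis and the sample size are not affected by this point. The conflict between prose and Table 3 over a discharge assessment of the primary outcome is a plain inconsistency and needs correcting whatever is decided about LOCF.

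**What to change.** 1. In Statistical analysis, replace LOCF as the supplementary analysis with multiple imputation carried out by arm. The imputation model should use admission scores, the scales that are collected at discharge, 3-month scores, centre and arrival-week cluster.
2. Preferably add a delta-adjusted version that worsens the imputed values in steps, to show how far the data would have to be missing not at random before the conclusion changes. The step sizes can be left to the analysis plan.
3. In Outcome measures, make the opening sentence and Table 3 agree on whether role functioning is assessed at discharge.

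The cost is a change of wording and a little more analysis work. No data are needed beyond those the trial already plans to collect. Recruitment was still under way when the article was published, so at that point the change could be fixed before outcomes were analysed.
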